# ADVERSE EVENTS

Adverse events (AEs) and Serious Adverse Events (SAEs) will be collected from baseline until the last patient’s evaluation. Investigators should monitor subjects for adverse events and are responsible for recording ALL adverse events and serious adverse events occurring to a patient during the trial.

An adverse event is any undesirable medical occurrence in a subject administered a pharmaceutical product and which does not necessarily have a causal relationship with this treatment. The time relationship is defined from the moment the AE occurs during therapeutic treatment until 30 days or 5 half-lives after treatment discontinuation. The adverse event may be a sign, a symptom, or an abnormal laboratory finding.

**Serious adverse events** (SAEs) must be reported to within 24 hours. If an adverse event meets any of the following criteria, it is considered SAE:

- **Life-threatening situation** The subject was at risk of death at the time of the adverse event/experience. It does not refer to the hypothetical risk of death if the AE were more severe or were to progress.
- **Inpatient hospitalization** or prolongation of existing hospitalization.
- **Persistent or significant disability/incapacity** Any AE having an outcome that is associated with a substantial disruption of the ability to carry out normal life functions, including the ability to work. This is not intended to include transient interruption of daily activities.
- **Congenital anomaly/birth defects** Any structural abnormality in subject’s offspring that occurs after intrauterine exposure to treatment.
- **Important medical events/experiences** that may not result in death, be life-threatening, or require hospitalization may be considered a serious adverse event/experience when, based upon appropriate medical judgment, **they may jeopardize the subject and may require medical or surgical intervention to prevent one of the outcomes listed above,** i.e., death, a life-threatening adverse event/experience, inpatient hospitalization or prolongation of existing hospitalization, a persistent or significant disability/incapacity, or a congenital anomaly/birth defect. Examples of such medical events/experiences include allergic bronchospasm requiring intensive treatment in an emergency room or at home, blood dyscrasias or convulsions that do not result in inpatient hospitalization, or the development of drug dependency or drug abuse.
- **Spontaneous and elective abortions** experienced by study subject.

**A non-serious adverse event** is any untoward medical occurrence in a patient or subject who is administered a pharmaceutical product, and which does not necessarily have a causal relationship with this treatment. A non-serious adverse event is one that does not meet the definition of a serious adverse event given.

***Grading of severity***

The severity of the adverse events shall be graded as:

- **Mild** the adverse event is transient and well tolerated by the patient
- **Moderate** the adverse events causes discomfort and affects the usual activities of the patient.
- **Severe** the adverse events affects the usual activities of the patient to an important degree and may cause disability or be life-threatening.

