## Study drug

The active study drug i.e. anakinra will be provided in the form of pre-filled ready-to-use syringes. All syringes need to be stored at 2-8°C at the study site at a refrigerator with recording of temperature. In case recording indicates deviation of temperature below 0°C or above 10°C for more than a day, stored syringes need to be replaced by the Sponsor. At the exterior of each syringe there will be a letter and a 4-digit number. The letter refers to the study site, the first two digits of the number refer to the serial number of enrolled patient at the respective study site and the last two digits refer to the day of treatment. For example, the code A0102 refers to study site A, patient number 01 at that study site and treatment day 2. In case of patients discharged earlier and continuing the drug by self-injection, pre-filled syringes will be provided in a cooling bag.

The adverse events of anakinra are classified as very common (≥ 1/10), common (≥ 1/100 to < 1/10) and uncommon (≥ 1/1,000 to < 1/100) and they are presented in the Table below^7^:

| **MedDRA Organ System** | **Frequency** | **Undesirable Effect** |
| --- | --- | --- |
| Infections and infestations | Common | Serious infections |
| Blood and lymphatic system disorders | Common | Neutropenia  Thrombocytopenia |
| Immune system disorders | Uncommon | Allergic reactions including anaphylactic reactions, angioedema, urticaria and pruritus |
| Nervous system disorders | Very common | Headache |
| Hepatobiliary disorders | Uncommon | Hepatic enzyme increased |
|  | Not known | Non-infectious hepatitis |
| Skin and subcutaneous tissue disorders | Very common | Injection site reaction |
|  | Uncommon | Rash |
| Laboratory | Very common | Blood cholesterol increased |

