## Patients’ visits and interventions (Appendix II)

*Day 1*

This visit will take place on the morning of the day of the start of treatment with the study drug. The following procedures will be done on that day:

- Recording of co-morbidities, co-administered drugs, past-history, SOFA score (Appendix III), absolute blood cell count and differential (if available) and biochemistry (if available)
- Scoring of the respiratory symptoms (Appendix IV).
- Administration of the study drug
- Recording of adverse events (AE) and severe adverse events (SAE)

*Day 2*

This visit will take place on the morning of the second day from the start of treatment with the study drug. The following procedures will be done on that day:

- Recording of co-administered drugs, absolute blood cell count and differential (if available) and biochemistry (if available)
- Recording of the presence or not of SRF (Appendix V)
- Recording of adverse events (AE) and severe adverse events (SAE)
- Administration of the study drug
- The visit may take place by phone call or through the internet in case of hospital discharge

*Day 3*

This visit will take place on the morning of the third day from the start of treatment with the study drug. The following procedures will be done on that day:

- Recording of co-administered drugs, absolute blood cell count and differential (if available) and biochemistry (if available)
- Recording of the presence or not of SRF (Appendix V)
- Recording of adverse events (AE) and severe adverse events (SAE)
- Administration of the study drug
- The visit may take place by phone call or through the internet in case of hospital discharge

*Day 4*

This visit will take place on the morning of the fourth day from the start of treatment with the study drug. The following procedures will be done on that day:

- Recording of co-administered drugs, absolute blood cell count and differential (if available) and biochemistry (if available)
- Recording of the presence or not of SRF (Appendix V)
- Recording of adverse events (AE) and severe adverse events (SAE)
- Administration of the study drug
- The visit may take place by phone call or through the internet in case of hospital discharge

*Day 5*

This visit will take place on the morning of the fifth day from the start of treatment with the study drug. The following procedures will be done on that day:

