- Recording of co-administered drugs, absolute blood cell count and differential (if available) and biochemistry (if available)
- Recording of the presence or not of SRF (Appendix V)
- Recording of adverse events (AE) and severe adverse events (SAE)
- Administration of the study drug
- The visit may take place by phone call or through the internet in case of hospital discharge

*Day 6*

This visit will take place on the morning of the sixth day from the start of treatment with the study drug. The following procedures will be done on that day:

- Recording of co-administered drugs, absolute blood cell count and differential (if available) and biochemistry (if available)
- Recording of the presence or not of SRF (Appendix V)
- Recording of adverse events (AE) and severe adverse events (SAE)
- Administration of the study drug
- The visit may take place by phone call or through the internet in case of hospital discharge

*Day 7*

This visit will take place on the morning of the seventh day from the start of treatment with the study drug. The following procedures will be done on that day:

- Recording of co-administered drugs, SOFA score (Appendix III), absolute blood cell count and differential (if available) and biochemistry (if available)
- Scoring of the respiratory symptoms (Appendix IV).
- Recording of the presence or not of SRF (Appendix V)
- Recording of adverse events (AE) and severe adverse events (SAE)
- Sampling of 15 ml of venous blood. Blood analysis will be done as described at the section Laboratory Procedures.
- Administration of the study drug
- The visit may take place by phone call or through the internet in case of hospital discharge. In that case, no blood sampling will take place.

*Day 8*

This visit will take place on the morning of the eighth day from the start of treatment with the study drug. The following procedures will be done on that day:

- Recording of co-administered drugs, absolute blood cell count and differential (if available) and biochemistry (if available)
- Recording of the presence or not of SRF (Appendix V)
- Recording of adverse events (AE) and severe adverse events (SAE)
- Administration of the study drug
- The visit may take place by phone call or through the internet in case of hospital discharge

*Day 9*

This visit will take place on the morning of the nineth day from the start of treatment with the study drug. The following procedures will be done on that day:

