Primary outcome and binary secondary outcomes as well as serious adverse event and adverse event rates between the two groups will be expressed as percentages and will be compared by the Fisher exact test, calculating also the respective odds ratios. The time to an event will be compared between the two groups by survival analysis. Stepwise Cox regression analysis will be conducted for the primary outcome and 30-day mortality. Quantitative secondary outcomes will be expressed as median values with respective interquartile range and will be compared by the Mann-Whitney U test.

The cost of hospitalization will be measured by adding the itemized cost of stay, drugs, and interventions and will be expressed as median with respective interquartile range. Salaries of nurse and medical stuff will not be included. Cost comparison will be done by the Mann-Whitney U test.

Qualitative baseline characteristics will be expressed as frequencies and percentages and compared by the Fisher exact test. Quantitative baseline characteristics will be expressed as mean values with standard deviation if following a normal distribution or median values with quartiles if following linear distribution. Comparisons of quantitative baseline characteristics will be done by the Student’s t-test or by the Mann-Whitney U test respectively. Paired comparisons will be done by the Wilcoxon’s rank-signed test. Non-parametric correlations will be done according to Spearman.

Analysis will be conducted with SPSS Version 25.0. All P values will be two-sided. Any P value <0.05 will be considered as statistically significant.

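### The drug's listed laboratory harms are recorded as values but never analysed as values, and the severity scale that would grade them has no laboratory criterion

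*Supplement*

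**What the plan says.** **Listed harms.** The side-effect table in the Study drug section of protocol version 3.0 has the rows "Blood and lymphatic system disorders | Common | Neutropenia" (thrombocytopenia stands in the same row) and "Hepatobiliary disorders | Uncommon | Hepatic enzyme increased". That section defines common as at least 1/100 and below 1/10, and uncommon as at least 1/1,000 and below 1/100. A low neutrophil count at entry is also an exclusion criterion.

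**Data collected.** The visit schedule has sites record "absolute blood cell count and differential (if available) and biochemistry (if available") on days 1 to 10 and day 14. From day 2, a discharged patient may be seen by phone or internet. For a remote day 7 visit the protocol adds: "In that case, no blood sampling will take place".

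**Route into the results.** Under Adverse Events, "The adverse event may be a sign, a symptom, or an abnormal laboratory finding". No threshold says when a value becomes an event.

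**Grading.** Under Grading of severity, Mild means that "the adverse event is transient and well tolerated by the patient". Moderate and Severe are defined by discomfort, effect on usual activities, disability and threat to life. There is no numeric criterion.

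**Analysis.** The SAP of 5 October 2020 states that "serious adverse event and adverse event rates between the two groups will be expressed as percentages" and compared by the Fisher exact test. Its only statement on population is that data are analysed by ITT. It plans no summary of laboratory values, no shift table and no count of patients tested.

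**The concern.** Low counts and raised liver enzymes often cause no symptoms, so they have to be found by measurement and graded by value. The plan collects the measurements and then relies on investigator-reported events, graded by how the patient feels and functions. Two weaknesses follow.

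1. **Grading.** The recorded grade of a silent laboratory abnormality says nothing about how far the value has moved.
2. **Coverage.** An event percentage over all patients does not separate those who were tested and normal from those who were not tested.

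At stake is whether a reader of the safety results can tell an absence of neutropenia, thrombocytopenia or liver-enzyme rise from an absence of measurement or of symptoms. The primary endpoint is not affected.

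**Working it through.** The plan gives no figure on this point, so there is none to reproduce. The grading part is a reading of the text. The coverage part is arithmetic on assumed coverage.

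**Grading, applied to a deep cytopenia without symptoms**

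- If it is transient, both conditions of Mild are met, whatever the count.
- If it persists, it is not transient, so it is not Mild. It causes no discomfort and does not affect activities, so it is neither Moderate nor Severe. No grade fits.
- If the investigator judges it serious, the Adverse Events section allows blood dyscrasias to be reported as SAEs. The section on relationship to the drug treats severity and seriousness as separate, so the grade stays as it was. Liver-enzyme rises are not among the SAE examples.

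**Coverage**

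Inputs:

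- *p*, true event rate: 1% to just under 10% for neutropenia or thrombocytopenia (the common band). 10% is used below as the limit, which the band itself excludes.
- *n* = 130, the size of the SAVE group in the only comparison that the SAP sets out.
- *t*, share of patients with at least one post-dose value: **not in the documents**. Range shown: 50% to 100%.
- Assumptions: testing is unrelated to risk, every abnormal value found is reported as an event, percentages are given by event type, and the denominator is all ITT patients. The SAP states none of these for laboratory events.

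Formulas: reported rate = *p* × *t*; expected cases = *n* × *p*; expected cases missed = *n* × *p* × (1 − *t*).

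| Share tested | Reported rate, *p* = 1% | Missed of 1.3 | Reported rate, *p* = 10% | Missed of 13 |
| --- | --- | --- | --- | --- |
| 100% | 1.00% | 0 | 10.0% | 0 |
| 90% | 0.90% | 0.13 | 9.0% | 1.3 |
| 75% | 0.75% | 0.33 | 7.5% | 3.25 |
| 50% | 0.50% | 0.65 | 5.0% | 6.5 |

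For 500 patients at 50% tested, the same formula gives 500 × 0.01 × 0.5 = 2.5 to 500 × 0.10 × 0.5 = 25 missed cases. For raised liver enzymes (uncommon band), 130 patients give 130 × 0.001 = 0.13 to just under 130 × 0.01 = 1.3 expected cases, so the absolute loss is below one case at any coverage in the range.

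**The case against.** **The grade enters no planned result.** The SAP compares event percentages, not percentages by grade. A silent cytopenia recorded as Mild still counts once. This stands: a reader might infer that the planned results would place events in the wrong severity class, but no table by grade is planned. The fault lies in the recorded grades and in any later table built from them.

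**Dangerous cytopenias have another route.** Blood dyscrasias may be reported as SAEs by medical judgment, and SAE rates are analysed. This stands in part. A reader might infer that severe silent cases simply disappear as Mild. That goes too far, because some may surface as SAEs and persistent ones do not meet Mild at all. But the route depends on judgment, leaves the grade unchanged and does not name liver enzymes.

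**The denominator is inferred.** A reader might take it as a rule of the SAP that untested patients count as event-free. No such rule is written. It follows only from the general ITT statement and the absence of any other denominator. Event incidence over all patients is also ordinary practice, and a tested-only rate has its own bias.

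**Coverage may be good.** Patients enter as hospital cases, and the SOFA score on days 1, 7 and 14 uses platelets and bilirubin, so some values should exist. Those not tested are probably the ones well enough to go home, in which case fewer cases would be missed than the table shows. This is fair. But SOFA contains neither neutrophils nor aminotransferases, its total does not report thrombocytopenia, and nothing in the plan would show the coverage achieved.

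**The yield is limited.** At 130 against 130, with true rates of 10% and 5% assumed and everyone tested, the two-sided Fisher test has only 24.7% power. Nor do the documents show that the comparators' registry holds serial post-baseline values. Both points stand: the gain is in description, not in a stronger test between groups. A reader might also infer that unequal testing distorts the group comparison. It could, but the documents give coverage for neither group.

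**Grading guidance may sit elsewhere.** The protocol mentions CRF completion instructions, which are not shown. They could hold laboratory grading rules, but neither the protocol nor the SAP refers to any.

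**Conclusion.** The concern holds in a limited form. Two parts rest on the text alone: the SAP plans no analysis of the recorded counts and biochemistry, and the severity scale cannot grade a laboratory abnormality by its depth. The coverage part rests on inference and on assumptions. If testing is unrelated to risk, the reported rate is anywhere from the true rate (all tested) down to half of it (half tested), which at 130 patients means from none to about 0.7 to 6.5 missed cases across the common band. The actual loss cannot be known, because the plan neither requires the tests nor reports how many patients had them. This is worth correcting because the harms are the protocol's own and most of the data are already collected.

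**What to change.** 1. **Protocol, Grading of severity:** state that laboratory adverse events are graded from the recorded value on a named standard numeric toxicity scale, and that the tolerance-based grades apply to clinical events.
2. **SAP, safety analysis, SAVE patients:** tabulate the worst post-dose value by numeric grade for neutrophils (lowest), platelets (lowest) and aminotransferases (highest), as a shift from day 1. Show the number tested on each day, and give rates over both patients with at least one post-dose value and all patients. Day 1 values are also recorded only if available, so show how many patients have a baseline value.
3. **Comparators:** extend the tables to them only where the registry holds serial values, and report coverage in each group beside any comparison.

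The cost is a few sentences and one or two tables from values that sites already record; no new tests are needed. The downside is that tested-only rates may overstate harm if sicker patients are tested more often, which is why both denominators should be shown.

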***Relationship to the drug***

The investigator will use the following definitions to assess the relationship of the adverse event to study drug:

- **Probably Related**: The adverse event has a strong time relationship to the drug or relapses if re-induced, and another etiology is improbable or clearly less probable.
- **Possibly Related**: The adverse event has a strong time relationship to the drug and an alternative aetiology is as probable or less probable.
- **Probably not Related**: The adverse event has a slight or no time relationship to the drug and/or there is a more probable alternative aetiology.
- **Unrelated**: The adverse event is due to an underlying or concomitant disease or to another pharmaceutical product and is not related to the drug (no time relationship and a much more probable alternative aetiology).

If an investigator’s opinion of possibly related, probably not related or not related to study drug is given, an alternate etiology must be provided by the investigator. Please note that a severe adverse event/experience is not necessarily serious, as the term severe is a measure of intensity while a serious adverse event is determined based on the aforementioned regulatory criteria. Individual un-blinding thought to be necessary for the management of an adverse event will be documented in the subject Case Report Form.

# QUALITY CONTROL AND ASSURANCE

Quality control and assurance checks are performed by sponsor in order to allow periodic review of adequacy of the study activities and practices and allow for revising such practices as needed so the data and process are maintained, the study meets the protocol and procedural requirements, and is reproducible.

Before enrolling any subject in this study, sponsor personnel and the investigator have to review the protocol, the IB, the CRFs and instructions for their completion, the procedure for obtaining informed consent and the procedure for reporting AEs and SAEs.

A qualified representative of the sponsor will monitor the conduct of the study by visiting the site and by contacting the site by telephone and e-mail. During these site visits, all source documents are reviewed, and information recorded in the CRFs is verified against them.

Besides routine monitoring, quality assurance will be documented through independent auditing of the quality control activities and where applicable, by regulatory authorities through inspections.

**ETHICAL CONSIDERATIONS**

Prior to the initiation of this study, the study design will receive ethical, scientific, and where applicable, regulatory review. Investigators will conduct this study in accordance with the principles of the Declaration of Helsinki, GCP, and applicable regulatory requirements.

Regarding Informed Consent Form obtaining procedures, before any procedure specified in the protocol is performed, a subject must:

- Be informed of all pertinent aspects of the study and all elements of informed consent
- Be given time to ask questions and to consider the decision to participate
- Voluntarily agree to participate in the study
- Sign and date the updated and approved by IEC/REB ICF version.

**PROTOCOL ADHERENCE AND AMENDMENTS**

Investigators ascertain that they will apply due diligence to avoid protocol deviations. All significant protocol deviations will be recorded and reported in the clinical study report (CSR). Any change or addition to the protocol can only be made in a written protocol amendment that must be approved and signed by the sponsor, health authorities where required, and the IEC/REB.

